### Inclusion and exclusion criteria

Inclusion criteria for the proposed data collection are: (1) being an EMaBS participant, (2) aged 18 or above, and (3) able to provide written and informed consent before taking part in this study. Potential participants who are clinically unwell will be asked to return when they have recovered. Exclusion criteria are current pregnancy, having been pregnant within the last 6 months, or already having a diagnosis of CVD or diabetes and being on medication (and hence physiological measures are influenced by this medication).

### Outcomes and exposures

The primary outcomes are physiological determinants of CVD measured in early adulthood, including systolic and diastolic blood pressure, blood lipid concentrations (total cholesterol, high-density lipoprotein cholesterol, low-density lipoprotein cholesterol and triglycerides), BMI, body composition measures (including fat mass and fat-free mass) and markers of glucose metabolism (fasting blood glucose, glycated haemoglobin (HbA1c) and insulin levels). Secondary outcomes include behavioural CVD risk factors, including unhealthy diet, physical inactivity, harmful alcohol use, current tobacco use and poor sleep, assessed using structured questionnaires. Qualitative outcomes include the understanding of CVDs, awareness of behavioural risk factors, perceived personal risk and sources of information on NCDs among participants.

The primary exposures of interest differ by objectives, as shown below.

For objectives 1 and 2a, exposures include early-life infectious exposures (malaria and helminth infections, including *Schistosoma mansoni* and soil-transmitted helminths, measured repeatedly from in utero through childhood), markers of early-life growth and undernutrition (birth weight and growth trajectories), micronutrient status in early childhood (iron indices, vitamin D, vitamin A, vitamin E, zinc, vitamin B12 and folate), inflammatory markers (C-reactive protein) and early-life socio-demographic characteristics (parental education, household socio-economic status and home environment indicators). Selected genetic variants derived from whole-genome data generated from samples collected in early childhood will be considered as secondary exposures.For objective 2b, behavioural risk factors assessed in adolescence and early adulthood (diet, physical activity, alcohol use, tobacco use and sleep quality) will be treated as exposures in analyses examining associations with physiological CVD determinants.For objective 3, analyses will focus on nutritional, infectious, metabolomic and socio-demographic pathways linking early-life exposures to physiological CVD risk in early adulthood. Findings from objective 1 will inform candidate pathways that will include longitudinal infection data, early-life micronutrient and inflammatory markers, metabolomic profiles derived from archived and newly collected samples, and early-life socio-economic conditions.

### Data collection

Participants will be invited to attend the study clinic once during the project period, at or near age 21 years. We will facilitate visits to the study clinic for participants residing both within and outside the original study area. Participants will attend two study visits. At the first visit (day 1), screening procedures will be conducted and written informed consent will be obtained. This visit will allow adequate time to explain the study procedures, including the fasting requirement, and to address any participant questions. The second visit (day 2) will involve the main study procedures and will be conducted after an overnight fast. Fasting blood samples will be obtained at the beginning of this visit, after which participants will be provided with a meal and refreshments as soon as possible.

We will collect data through questionnaires and physical examination. Questionnaires will be used to update existing socio-demographic information for each participant, collect information on current living conditions, family composition, level of education attained and occupation, and collect information on behavioural risk factors for NCDs, including physical activity, diet, alcohol use, tobacco use, mental health, sleep quality and well-being. Tobacco use will be assessed through self-report, including current and previous smoking status, and number of pack-years. Alcohol use will be assessed through the 30-day Alcohol Use Disorders Identification Test (AUDIT-40), which has been validated against the Timeline Follow Back method, and against phosphatidylethanol in blood for detecting harmful alcohol use in Ugandan youth.^12^ Physical activity will be assessed using the WHO Global Physical Activity Questionnaire, which has been shown to have moderate to high validity and reliability across 12 countries worldwide and was previously used in a Ugandan countrywide survey.^13^ Diet and nutrition will be assessed through food frequency questionnaires, which will include commonly consumed food items from the Uganda regional food surveys; energy and nutrient content will be calculated from available food composition tables; we will focus on high intake of sugar, salt and fat, low intake of fruits and vegetables, and high intake of processed foods. Common mental health disorders will be assessed using the Patient Health Questionnaire−9^14^ and the generalised anxiety disorder−2.^15^ Sleep quality will be assessed using the insomnia severity index.^16^

The physical examination will include measurements of height, weight, waist circumference, blood pressure and body composition. Participants will be measured wearing light clothing and without shoes. Height will be measured to the nearest centimetre, and weight to the nearest 0.1 kg. Waist circumference will be measured at the mid-way position between the lowest rib and the iliac crest and recorded to the nearest centimetre. Body composition will be measured using a Tanita body composition analyser (MC-580M S, TANITA Corporation, Tokyo, Japan). Trained nurses will measure blood pressure three times, 3 min apart, using an appropriately sized cuff on the right arm, supported at heart level, with the participant seated upright all the way to the back of the chair, legs uncrossed and feet flat on the floor. Automated Omron (Kyoto, Japan) (M6, HEM-700) machines validated every 6 months by the Uganda National Bureau of Standards will be used. The mean of the second and third measurements will be used for analysis. We will also obtain fasting blood (as early in the visit as possible), stool samples and urine (only from female participants for pregnancy testing at screening).

To better understand social and behavioural factors that may influence the risk of CVD in individuals and collect initial data on the nature of acceptable interventions, we will also conduct 50 qualitative in-depth interviews and five focus group discussions. Participants for the in-depth interviews and focus group discussions will be purposively sampled from those who are enrolled in the study. We will use maximum variability sampling to obtain a heterogeneous sample. All interviews will be audio-recorded with consent and guided by a semi-structured topic guide.

### Laboratory methods

Lipid parameters will be measured in fasting blood serum using a homogeneous enzymatic colourimetric assay. Blood glucose and insulin sensitivity will be measured in fasting venous blood samples, with insulin sensitivity estimated using the Homeostasis Model Assessment of Insulin Resistance, and HbA1c will be measured using a turbidimetric inhibition immunoassay. All biochemical analyses will be performed using a Roche (Roche Diagnostics Ltd, Burgess Hill, United Kingdom) Cobas 6000 platform (c 501 module) at the Clinical Diagnostics Laboratory based at MRC/UVRI and LSHTM Uganda Research Unit. A portion of the blood sample will be used for a complete blood count and examined for malaria by PCR and for *S. mansoni* by circulating anodic antigen. The rest of the blood will be used for peripheral blood mononuclear cell separation to allow for investigation of cellular immune responses.

Stool samples will also be collected from the participants to enable measurement of helminth infections using PCR, and for investigation into the link between the gut microbiome and CVD risk in a longitudinal framework. Among subgroups of participants selected based on phenotypic extremes (exposure and outcome), further detailed phenotyping will be undertaken, guided by which early-life exposures are associated with which physiological determinants of CVDs, to investigate potential pathways for these associations. Based on our earlier data showing that biological pathways associated with cholesterol metabolism are significantly enriched in *S. mansoni*-infected participants compared with uninfected participants,^17^ we plan to extract metabolites from new serum samples collected from participants and from stored samples collected in childhood. Metabolites will be profiled using liquid chromatography mass spectrometry at the Biological Mass Spectrometry Core Research Facility at the University of Manchester. Blood and serum samples will be stored to enable future work, including epigenetic studies, to be designed based on the findings of the proposed work.

### Data management

Data will be captured electronically and managed using Research Electronic Data Capture (REDCap) electronic data capture tools hosted at MRC/UVRI. All data, including audio recordings, will be anonymised and stored on a secure and password-protected server, with access limited to essential research personnel. Data and samples will be labelled with the unique identification number of each participant to enable linkage with historical data. To ensure data quality and reliability, clinical and laboratory procedures will follow standard operating procedures. Range checks will be programmed into data collection tools in REDCap. The study will be regularly monitored and conducted in accordance with Good Clinical Practice and Good Clinical Laboratory Practice principles. Qualitative interviews will be audio-recorded using an encrypted digital recording device that is kept on the researcher’s person at all times. Audio files will be uploaded to a secure server as soon as possible after the interview and thereafter deleted from the audio device. No identifying information will be recorded. Audio recordings will be transcribed verbatim and stored on a secure server. When in use, transcripts will be analysed on an encrypted laptop, either in the custody of a researcher or in a safe location at the MRC/UVRI and LSHTM Uganda Research Unit offices.

### Sample size determination

Our target minimum sample size is 900 participants. Our preliminary data suggest that blood pressure will be normally distributed with SD in the range 8–10 mmHg, and that lipid parameters will be normally distributed (or amenable to normalisation by log-transformation) with SD in the range 0.4–0.8 mmol/L. Our key early-life exposures of interest will have variable distributions and prevalence. Table 1 shows mean differences in outcome between exposed and unexposed groups that we will have 80% power to detect at a 5% significance level across a range of exposure prevalence, with adjustment for confounders.

**Table 1 T1:** Power estimates for the effect of exposures on primary outcomes (objectives 1 and 2)

	SD for blood pressure outcomes, mmHg					SD for lipid parameter outcomes, mmol/L				
Exposure prevalence	8	8.5	9	9.5	10	0.4	0.5	0.6	0.7	0.8
5%	3.7	3.9	4.2	4.4	4.6	0.19	0.23	0.28	0.32	0.36
10%	2.8	2.9	3.1	3.3	3.4	0.14	0.18	0.21	0.24	0.27
20%	2.2	2.3	2.4	2.5	2.6	0.12	0.14	0.16	0.18	0.21
30%	1.9	2.0	2.1	2.2	2.3	0.11	0.12	0.14	0.16	0.18
40%	1.8	1.9	2.0	2.1	2.2	0.10	0.12	0.13	0.15	0.17
50%	1.8	1.9	2.0	2.1	2.2	0.09	0.11	0.13	0.15	0.17

No formal adjustment for multiplicity is planned; we shall analyse a pre-specified set of exposures and outcomes and focus on patterns and consistency of results. The target sample size ensures sufficient power to detect small-to-moderate differences in mean outcome (<4 mmHg for blood pressure (BP) and <0.3 mmol/L for lipid parameters).

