#### Objective 1: to determine the effect of early-life exposures on physiological determinants of CVDs measured in young Ugandan adults

We will use regression analysis to assess associations with our primary exposures of interest—namely infections and growth/undernutrition—across specific life-course exposure periods. For continuous outcomes, we will use linear regression models to assess associations between each exposure and each outcome, adjusting for confounders. For binary outcomes, logistic regression models will be used to determine the effect of each exposure on the outcome, adjusting for confounders. First, exposures will be modelled individually at each time point to examine cross-sectional associations with the outcomes. Where exposure data have been collected repeatedly over time, such as for malaria and *S. mansoni* infections, we will explore trajectories of exposure and their relationships with study outcomes using latent class or trajectory analysis. Repeated binary measures will also be analysed as time-varying covariates in mixed-effects models.

Additionally, we will leverage longitudinal data collected on the same outcome measures at age 10–11 years, which will also enable the inclusion of participants with some missing time-point data. Causal modelling approaches will be used to obtain unbiased estimates of the average causal effect of each early-life exposure on each outcome, adjusting for confounders. For each exposure-outcome relationship, we will construct directed acyclic graphs to identify the minimal sufficient set of confounders. Inverse probability weighting will be applied to create a pseudo-population in which exposure is independent of measured confounders, thereby enabling adjustment for selection bias due to differential loss to follow-up or missing outcome data. We will also explore secondary exposures of interest, including selected genetic variants from existing whole-genome data that have been linked to CVD risk in other populations.

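### Table 1's confounder-adjusted detectable differences do not scale with SD in six of twelve rows and imply a different adjustment at each prevalence

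*Protocol article*

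**What the plan says.** The section Sample size determination in the Protocol article states: "Our target minimum sample size is 900 participants". It assumes that "blood pressure will be normally distributed with SD in the range 8–10 mmHg" and gives lipid parameters, log-transformed if need be, "with SD in the range 0.4–0.8 mmol/L". On exposures it says: "Our key early-life exposures of interest will have variable distributions and prevalence". Then "Table 1 shows mean differences in outcome between exposed and unexposed groups", described as those for which the study will have "80% power to detect at a 5% significance level across a range of exposure prevalence, with adjustment for confounders". The table has six prevalences (5% to 50%) and five SDs for each of blood pressure (BP) and lipids, 60 cells in all. No R-squared, VIF or formula for the adjustment appears. The section ends by claiming enough power for "small-to-moderate differences in mean outcome (<4 mmHg for blood pressure (BP) and <0.3 mmol/L for lipid parameters". The analysis being powered is set out under Objective 1: "we will use linear regression models to assess associations between each exposure and each outcome, adjusting for confounders".

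**The concern.** In a linear model, adjusting for confounders multiplies the standard error of the exposure coefficient by the square root of VIF = 1/(1 − R-squared of exposure on confounders). Two things follow. Along a row of Table 1, the detectable difference should be a constant multiple of SD. Down a column, if one adjustment is assumed throughout, each cell should be the same multiple of its unadjusted value. Some rows fail the first test and the columns fail the second.

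Table 1 is the only power statement in the article, and the closing claim rests on it. If the allowance for confounding is not the same from row to row, a reader cannot compare rare with common exposures. The rare ones, where power is weakest, have the smallest proportional allowance.

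**Working it through.** **Inputs** (Sample size determination): n = 900, power 80%, significance 5%, p = 5% to 50%, SD = 8 to 10 mmHg and 0.4 to 0.8 mmol/L. Two-sided testing is assumed, as the article does not say.

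**Formula.** Unadjusted difference = (1.960 + 0.842) × SD / sqrt(900 p(1−p)); adjusted = unadjusted × sqrt(VIF).

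**Step 1: reproduce the table.** No printed cell equals its unadjusted value; all 60 are larger. The multiplier range below is the set of values of sqrt(VIF) that would reproduce all five cells of a row after rounding.

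| BP, prevalence | Unadjusted, SD 8 / 10 | Printed, SD 8 / 10 | Multiplier range | VIF |
|---|---|---|---|---|
| 5% | 3.43 / 4.28 | 3.7 / 4.6 | 1.076–1.085 | 1.16–1.18 |
| 10% | 2.49 / 3.11 | 2.8 / 3.4 | 1.104–1.108 | 1.22–1.23 |
| 20% | 1.87 / 2.33 | 2.2 / 2.6 | none (≥1.151 and ≤1.135) | none |
| 30% | 1.63 / 2.04 | 1.9 / 2.3 | 1.135–1.153 | 1.29–1.33 |
| 40% | 1.52 / 1.91 | 1.8 / 2.2 | 1.148–1.180 | 1.32–1.39 |
| 50% | 1.49 / 1.87 | 1.8 / 2.2 | 1.171–1.205 | 1.37–1.45 |

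| Lipids, prevalence | Multiplier must be at least | and at most | Fits? |
|---|---|---|---|
| 5% | 1.079 | 1.065 | no |
| 10% | 1.124 | 1.104 | no |
| 20% | 1.231 | 1.132 | no |
| 30% | 1.288 | 1.135 | no |
| 40% | 1.246 | 1.148 | no |
| 50% | 1.138 | 1.171 | yes (VIF 1.29–1.37) |

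**Step 2: scaling with SD.** This needs only the printed cells.

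- BP at 20%: 2.2/8 is at least 2.15/8 = 0.269, but 2.6/10 is at most 2.65/10 = 0.265.
- Lipids at 30%: SD doubles from 0.4 to 0.8, but the difference goes from 0.11 to 0.18, not 0.22.
- Six of twelve rows fail: BP 20% and lipids 5%, 10%, 20%, 30% and 40%. The other five BP rows and the lipid 50% row scale within rounding.

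**Step 3: one inflation for all rows.** The BP multiplier ranges at 5% and 50% do not overlap. Equivalently, under any common multiplier the 5% cell divided by the 50% cell should be sqrt(0.25/0.0475) = 2.29. The BP half gives 3.7/1.8 = 2.06 at SD 8 and 4.2/2.0 = 2.10 at SD 9, and at most 4.25/1.95 = 2.18 with rounding. The best single multiplier reproduces 15 of 30 BP cells (1.172) and 18 of 30 lipid cells (1.132).

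**Step 4: a pattern that does fit.** Unadjusted + 0.3 mmHg reproduces 30 of 30 BP cells. Unadjusted + 0.02 mmol/L reproduces 28 of 30 lipid cells; the exceptions, both at SD 0.4, are 20% (0.093 + 0.02 = 0.113, printed 0.12) and 30% (0.082 + 0.02 = 0.102, printed 0.11).

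**Step 5: size, in both directions.**

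- The BP 50% row's VIF of about 1.4 applied to the BP 5% row: 3.43 × 1.183 = 4.1 at SD 8 and 4.28 × 1.183 = 5.1 at SD 10 (printed 3.7 and 4.6).
- The lipid 50% row's own VIF, 1.29 to 1.37, applied to the lipid 5% row: 0.171 × 1.138 to 1.171 gives about 0.20 at SD 0.4, and 0.343 × the same gives 0.39 to 0.40 at SD 0.8 (printed 0.19 and 0.36).
- The BP 5% row's VIF of 1.16 to 1.18 applied to the BP 50% row: 1.49 × 1.08 = 1.6 and 1.87 × 1.08 = 2.0 (printed 1.8 and 2.2).

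**The case against.** **VIF may vary with prevalence.** The R-squared of a binary exposure on its confounders can differ between rare and common exposures, and the article does not promise a single VIF. This stands as far as it goes: Step 3 shows only that no common inflation was used. It does not explain Step 2, because the VIF depends on exposure and confounders and cannot change with the outcome SD within a row. Nor can a different true n, one-sided testing or a proportionate fall in residual SD, each of which multiplies a whole row by one factor.

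**Rounding.** The lipid cells have two decimals, so 0.11 at SD 0.4 carries about 5% rounding error. That matters for lipids at 30%: without that cell the row just fits (0.115/0.5 = 0.230 against 0.185/0.8 = 0.231). The other four lipid rows fail even without their SD 0.4 cells, for example 40% (0.115/0.5 = 0.230 against 0.175/0.8 = 0.219), although 5% misses narrowly (0.275/0.6 = 0.458 against 0.365/0.8 = 0.456).

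**Detail left to a fuller protocol.** An omitted R-squared would be no fault in an article. The fault is that printed numbers conflict with each other whatever R-squared was used.

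**A stronger reading.** A reader might infer that the low-prevalence rows are wrong and the study is underpowered for rare exposures. The article does not support that. No row is a reference, every cell exceeds its unadjusted value, and taking the BP 5% row as correct makes the BP 50% row conservative. It would also be too much to say that no row scales with SD, since six do.

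**Small consequence.** Under Study populations and recruitment, all available eligible participants are to be sampled, so a corrected table would not alter recruitment. This stands and limits the weight of the point.

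**Conclusion.** The point holds in a limited form. Table 1 is not consistent with the regression adjustment that it claims: six of twelve rows break proportionality with SD beyond rounding, and the BP rows imply VIFs from about 1.16–1.18 at 5% prevalence to 1.37–1.45 at 50%. The within-row result rests on no assumption about n, sidedness or R-squared. The comparison between rows assumes that one adjustment was intended. That a constant was added to the unadjusted values is an inference from the fit.

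The direction is relative only: either the rare-exposure figures are optimistic, by roughly 0.4 to 0.5 mmHg and 0.01 to 0.04 mmol/L in the 5% row, or the common-exposure figures are conservative, by about 0.2 mmHg in the BP 50% row. The first case bears on the closing claim. At the 50% row's inflation, all five BP cells at 5% prevalence reach about 4 mmHg or more. As printed, that row already exceeds 4 mmHg at SD 9 to 10 (4.2, 4.4, 4.6) and 0.3 mmol/L at SD 0.7 and 0.8 (0.32, 0.36). That is a separate mismatch which needs no VIF argument.

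**What to change.** State the assumed R-squared of exposure on confounders, or the VIF, as one value or a short range. Recompute every cell as 2.80 × SD × sqrt(VIF / (900 p(1−p))). As an illustration with assumed values, R-squared of 0.1, 0.2 or 0.3 gives 3.6, 3.8 or 4.1 mmHg at 5% prevalence and SD 8, and 1.6, 1.7 or 1.8 mmHg at 50%. If a VIF that varies with prevalence is intended, give it for each row. Then restate the closing claim of less than 4 mmHg and less than 0.3 mmol/L to match the new cells, naming the prevalence and SD at which it holds.

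The cost is one table and one sentence. The figures for rare exposures may become less favourable; those for common exposures may improve slightly. The target of 900, the design and the analysis are unaffected.

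### The claim that 900 participants give sufficient power below 4 mmHg and 0.3 mmol/L does not hold in half of Table 1's 5% prevalence row (minor wording error)

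*Protocol article*

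**What the plan says.** All the relevant text is in the protocol article under Sample size determination.

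- Target: "Our target minimum sample size is 900 participants".
- Assumed spread: "blood pressure will be normally distributed with SD in the range 8–10 mmHg", and lipid parameters "with SD in the range 0.4–0.8 mmol/L".
- Exposures: "Our key early-life exposures of interest will have variable distributions and prevalence". No prevalence is given for any named exposure.
- Table 1 is introduced as showing the "mean differences in outcome between exposed and unexposed groups that we will have 80% power to detect at a 5% significance level", after adjustment for confounders, for prevalences of 5% to 50%.
- The 5% row of Table 1 reads "3.7 3.9 4.2 4.4 4.6 0.19 0.23 0.28 0.32 0.36". The first five values are mmHg at SD 8, 8.5, 9, 9.5 and 10. The last five are mmol/L at SD 0.4, 0.5, 0.6, 0.7 and 0.8.
- The section closes by saying that the target ensures "sufficient power to detect small-to-moderate differences in mean outcome (<4 mmHg for blood pressure (BP) and <0.3 mmol/L for lipid parameters").

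The closing sentence carries no condition on prevalence or SD, and nothing elsewhere in the article supplies one.

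**The concern.** A sentence that summarises a power table should be true of that table. The natural reading of this one is that, across the planning assumptions, the difference detectable with 80% power stays below 4 mmHg and below 0.3 mmol/L. In the 5% row it does not for the upper part of either SD range, and for blood pressure the failing part includes the midpoint, SD 9.

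The sentence is the stated justification for 900 participants and is what later readers are likely to cite. The analysis plan for Objective 1 models exposures one time point at a time and also derives latent classes or trajectories from repeated infection data, so small exposed groups are possible. For such an exposure, someone relying on the sentence would believe that power for a 4 mmHg difference was at least 80% when the article's own table puts it lower.

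**Working it through.** **Inputs** (Sample size determination and Table 1): N = 900; 80% power; 5% significance, taken as two-sided because the article does not say; SD 8–10 mmHg and 0.4–0.8 mmol/L; prevalence q = 5%, so 45 exposed and 855 unexposed.

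**1. Direct comparison.** This needs no calculation.

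| Row of Table 1 | Cells at or above 4 mmHg | Cells at or above 0.3 mmol/L |
|---|---|---|
| 5% | 3 of 5 (4.2, 4.4, 4.6) | 2 of 5 (0.32, 0.36) |
| 10% | 0 of 5 (largest 3.4) | 0 of 5 (largest 0.27) |
| 20% to 50% | 0 of 20 | 0 of 20 |

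Five of 60 cells break the stated limits, all in one row.

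**2. Attempt to reproduce the row.** Without adjustment, the detectable difference is

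(z₀.₉₇₅ + z₀.₈₀) × SD / √(N q (1 − q)) = 2.8016 × SD / √(900 × 0.05 × 0.95) = 2.8016 × SD / 6.538.

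| | BP SD 8 | 8.5 | 9 | 9.5 | 10 | Lipid SD 0.4 | 0.5 | 0.6 | 0.7 | 0.8 |
|---|---|---|---|---|---|---|---|---|---|---|
| Unadjusted | 3.43 | 3.64 | 3.86 | 4.07 | 4.29 | 0.171 | 0.214 | 0.257 | 0.300 | 0.343 |
| Table 1 | 3.7 | 3.9 | 4.2 | 4.4 | 4.6 | 0.19 | 0.23 | 0.28 | 0.32 | 0.36 |

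The printed values are 5% to 11% larger. That is the expected direction, since they include confounder adjustment, but the size of the adjustment is not stated, so the row cannot be reproduced exactly. No single multiplicative factor reproduces the whole table either (the best matches 28 of 60 cells). I therefore take the printed values as given. Even without adjustment, SD 9.5 and 10 (4.07 and 4.29 mmHg) and SD 0.8 (0.343 mmol/L) miss the limits, and SD 0.7 sits on 0.300.

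**3. Power implied by Table 1's own values.** A difference detectable with 80% power equals 2.8016 standard errors, so SE = table value / 2.8016, and power for a difference Δ is Φ(Δ/SE − 1.96).

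| Cell | SE | Δ/SE − 1.96 | Power |
|---|---|---|---|
| SD 9, 4.2 mmHg; Δ = 4 | 1.499 | 0.71 | 76% |
| SD 9.5, 4.4 mmHg; Δ = 4 | 1.571 | 0.59 | 72% |
| SD 10, 4.6 mmHg; Δ = 4 | 1.642 | 0.48 | 68% |
| SD 0.7, 0.32 mmol/L; Δ = 0.3 | 0.1142 | 0.67 | 75% |
| SD 0.8, 0.36 mmol/L; Δ = 0.3 | 0.1285 | 0.37 | 65% |

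The same calculation gives 86% and 82% for 4 mmHg at SD 8 and 8.5, and more than 99%, 96% and 85% for 0.3 mmol/L at SD 0.4, 0.5 and 0.6. Those five cells support the sentence.

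**The case against.** The strongest reply is that the sentence is a fair gloss on a table printed directly above it. Fifty-five of 60 cells agree with it, the exceptions sit in the lowest-prevalence row at the larger SDs, and the larger values are openly shown. All of that stands, and it makes the point minor. It does not make the sentence true: it says the target ensures the power, without condition, and 5% prevalence is one of the authors' own planning scenarios.

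A second reply is that 900 is a minimum. Study populations and recruitment describes taking as many participants as are available, with about 1500 having given contact details and 976 seen at 15–18 years. More participants would help: scaling the worst cells, 900 × (4.6/4)² ≈ 1190 and 900 × (0.36/0.3)² = 1296 would bring the detectable differences down to the two limits. But the sentence is about the target, and the strengths and limitations box names reaching that target as a potential challenge.

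Third, nothing in the article plans to read a null result as excluding 4 mmHg. It plans effect estimates and a focus on patterns and consistency, and it does not say that any key exposure has a prevalence near 5%. This also stands, so the harm is possible and not shown.

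A reader might go further than the documents allow in three ways:

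- **That 900 is the wrong target.** Table 1 supports the limits throughout from 10% prevalence upwards, so the summary is at fault and not the target.
- **That no exposure below 10% prevalence is adequately powered.** Half of the 5% row meets the limits, and 10% is simply the next row of the table, not the point at which the claim starts to hold.
- **That a precise cut-off can be worked out from a variance inflation of about 1.4.** The article gives no inflation factor. A value of that size resembles the 50% row, where (1.8/1.49)² ≈ 1.45, but at the largest SDs the 5% row implies only (4.6/4.29)² ≈ 1.15 and (0.36/0.343)² ≈ 1.10.

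**Conclusion.** The closing sentence is wrong as written, and the error is minor. At 5% exposure prevalence, 900 participants do not give 80% power for differences below 4 mmHg when the SD is 9 or more, or below 0.3 mmol/L when the SD is 0.7 or more. Power in those cells is about 68% to 76% for 4 mmHg and 65% to 75% for 0.3 mmol/L: short of 80%, but far from absent.

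The contradiction itself rests only on the printed table. The power figures assume a two-sided 5% test, a normal approximation, and the table values as rounded in print. Rounding moves them by about one percentage point: a printed 4.2 could be 4.15 to 4.25, which gives SE 1.481 to 1.517 and power 77% to 75%. How far the point matters in practice depends on the actual exposure prevalences, which the article does not report.

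**What to change.** Replace the closing sentence with one that follows the table, for example:

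> For exposures with prevalence of at least 10%, 900 participants give 80% power for differences of at most 3.4 mmHg and 0.27 mmol/L across the assumed SD ranges; at 5% prevalence the detectable differences are 3.7–4.6 mmHg and 0.19–0.36 mmol/L, depending on the SD.

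Every figure is already in Table 1. The cost is one sentence and a slightly less favourable headline. The target, the design and the analyses stay as they are, and no special reporting rule for uncommon exposures is needed.
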